**S1. Protocol in English**

**Effect of early measles vaccine on pneumococcal colonization: A randomized trial from Guinea-Bissau**

**Summary**

Recent studies from Guinea-Bissau and Denmark have shown that measles vaccine (or measles-mumps-rubella vaccine in Denmark) protects children against lower respiratory infections.

*Streptococcus pneumoniae* is a leading cause of lower respiratory infections. In the present studywe investigate effect of providing an early MV at age 4.5 months on the risk of nasopharyngeal colonization with *S. pneumoniae* in children in Guinea-Bissau. We hypothesize that early MV reduces the carriage rate from 85% to 75%. Within a randomized clinical trial of early MV we will enroll 420 children who receive an early MV and 210 controls who receive no early MV. All children will have a nasopharyngeal swab performed immediately before randomization at 4.5 months of age and eight weeks after, as well as by 9 months of age, immediately before the recommended MV. Colonization with *S. pneumoniae* will be determined by quantitative PCR.

**Background**

Many observational studies in different countries1,2 and a randomized trial in Guinea-Bissau3 have shown beneficial effects of measles vaccine (MV) on child survival which are independent of its direct effect of preventing measles. In the randomized trial the mortality rate ratio (MRR) of children given MV at 4.5 and 9 months of age compared to those given a single dose at 9 months of age was 0.70 (0.52-0.94), independently of the protective effect on measles infection3. Analysis of a subgroup of children showed that children with maternal measles antibody at the time of the first MV had a markedly enhanced survival rate (MRR 0.17; 0.05-0.58) compared to children given the first MV when maternal measles antibody was absent (Aaby et al, submitted).

Analysis of hospital admissions showed a reduction in early MV group, which was strongest for pneumonia/respiratory infections; the admissions hazard ratio was 0.37 (0.37; 0.16-0.89) compared with the controls (Aaby et al, submitted). This finding was recently supported in a register-based study among Danish children, in which measles-mumps-rubella vaccination was associated with a 21% (95% CI 17-24%) reduction in the risk of lower respiratory infections (Sørup et al, submitted). It should be noted that these findings were done in situations where

1

there was no circulating measles virus and thus were unrelated to the measles-preventive effect of the vaccine.

Preliminary studies in The Gambia suggest that measles vaccine may reduce nasopharyngeal carriage of *S. pneumoniae*. These observations fit with strong evidence from animal studies that priming with one pathogen may induce heterologous immunity and thus reduce susceptibility to subsequent infection with another unrelated pathogen4,5.

Globally, *S. pneumoniae* infections are a leading cause of pediatric morbidity and mortality; it is estimated that *S. pneumoniae* is responsible for more than 800,000 deaths and nearly 15 million severe infections, including pneumonia, annually in children below 5 years of age, with 90% of cases occurring in low-income countries6. Asymptomatic nasopharyngeal colonization is considered to be the first step in the pathway to infection7. Children in low-income settings experience early and abundant *S. pneumoniae* carriage very early in life8. Pneumococcal conjugate vaccines prevent invasive infections, but have not yet been implemented in many poor countries, including Guinea-Bissau.

At the Bandim Health Project in Guinea-Bissau, a large randomized trial examining the impact of maternal antibody on the non-specific effects of measles vaccine is in progress. Normally children receive MV at 9 months of age. In the trial infants are randomized 2:1 to two doses of MV at 4.5 and 9 months of age or a single MV at 9 months of age. All children have blood collected at enrolment for assessment of maternal antibody levels. Mortality and the frequency of hospital admissions will be compared between the groups overall and within the periods 4-8 months and 9-36 months. The data will be analyzed according to presence of maternal measles antibody at 4.5 months to test the hypothesis that early MV is particularly beneficial when given in the presence of maternal antibodies.

We propose that one of the mechanisms by which early MV exerts its beneficial non-specific effects on mortality and the risk of hospital admissions for respiratory infections is by reducing the carriage of *S. pneumoniae*. Thus, within the main trial we have designed a sub study to test the hypothesis that early MV reduced the risk of being colonized with *S. pneumoniae*.

2

**Methods**

In the capital Bissau, the Bandim Health Project (BHP) is running a health and demographic surveillance system which covers more than 102,000 individuals in 6 suburbs. All residents are given a unique identification number and information on background factors including socio-economic factors is collected. All houses in the BHP study area are visited monthly by an assistant who registers new pregnancies and births. Once a newborn is identified, the child is followed with trimonthly visits until 3 years of age. Information on vital status and vaccination status is registered at each visit.

***Study design***

The present study is nested within the Early MV trial, a randomized controlled trial (RCT), which was initiated in August 2011 and will continue to enroll children until a sample size of 6600 children is reached, anticipated by the end of 2014. A subgroup of the participants in the trial will be invited to participate in the present study.

***The Early MV trial***

The primary objective of the early MV trial is to study the effect of early MV at 4.5 months versus no early MV at 4.5 months on overall mortality until 36 months of age. All children receive the recommended MV at 9 months. Inclusion criteria are that the child has received the third dose of pentavalent vaccines recommended at 14 weeks of age, at least four weeks before enrolment. Provided oral and written consent from the mother/guardian, the child is examined clinically to identify ill children in need of hospitalization, children with malformations impairing health and malnourished children (defined as a mid-upper-arm circumference (MUAC) less than 115 mm). These infants are temporary excluded, but are invited to be enrolled in the study when they have recovered.

A blood sample is obtained for determination of maternal measles antibody levels. All children who are invited to participate are offered free consultations at the local health centers and essential drugs free of charge. A questionnaire is filled out, covering the health of the child and socio-economic factors.

3

Infants are randomized by block randomization procedures, stratified by sex. Each envelope contains 24 lots, 2/3 of the lots assign the child to the intervention group (early MV), 1/3 of the lots assign the child to the control group (no early MV). Twins of the same sex are allocated to the same treatment to avoid confusion. Children randomized to early MV receive a single dose of 0.5 ml MV (Edmonston-Zagreb strain, Serum Institute of India) as a subcutaneous injection into the upper part of their back. No placebo is given, since mothers could get the false impression that their child was measles vaccinated.

***The pneumococcal sub-study***

*Objective*

In a subset of children we will test the effect of early MV on *S. pneumoniae* carriage. Thus, 420 children randomized to MV and 210 controls randomized to no MV will have a nasopharyngeal swab performed immediately before randomization, and at 6.5 and again at 9 months of age (immediately before MV) and colonization with *S. pneumoniae* will be determined (Figure 1).

[figure not shown]

*Hypothesis*

We hypothesize that early MV at 4.5 months of age is associated with a reduction in the risk of being colonized by *S. pneumoniae* at 6.5 and 9 months of age.

4

*Nasopharyngeal swabs*

Nasopharyngeal specimens will be obtained following a set protocol. A small, flexible, swab is inserted into one of the nares to the level of the posterior nasopharynx, a distance approximately midway between the tip of the nose and the ear lobe9,10. Swab specimens will be

placed in a labeled vial containing 1 ml skim milk-tryptone-glucose-glycerin (STGG) medium and transported on ice to the laboratory within three hours9. A 0.5 ml aliquot of the sample will be mixed with a DNA/RNA stabilizing transport medium for future molecular testing. The samples will be frozen at -40°C and will be transported to Statens Serum Institut, Denmark, for further processing.

*Detection of* S. pneumoniae *by quantitative PCR*

PCR will be performed to determine the total load of pneumococci using a quantitative real-time PCR method detecting a specific segment of the autolysin gene (*lyt*A) and incorporating an internal control to monitor inhibition.

*Further studies on the collected specimens*

For the present study the quantitative PCR results will be used. Remnants of the extracted DNA and original samples will be stored at SSI. Should funding become available, we will also test it for the presence of other pathogens and for changes in the microbial flora. Furthermore, should funding become available, the sample in the STGG medium will be used for culture and serotyping of pneumococci, providing pre-vaccination baseline data on pneumococcal serotype distribution in Guinea-Bissau.

*Statistical analysis*

Analyses will be conducted on the basis of intention to treat using Stata. Baseline characteristics of the treatment groups will be compared using chi square tests for contingency data and t tests for continuous data. Multivariate Poisson models with robust variance estimation providing prevalence ratios (PR) will be used to evaluate the effect of early MV overall and stratified by potential effect modifiers: sex and presence of maternal antibodies. Differences will be considered significant at P<0.05.

5

*Sample size calculations*

The prevalence of *S. pneumoniae* carriage in Guinea-Bissau is unknown, but based on data from similar areas12,13 we assume that the prevalence in the control group will be 85% and with 420 children in the intervention group and 210 children in the control we will be able to show a reduction from 85% to 75% associated with early MV with a power of 80% and p<0.05. We have chosen to keep the 2:1 ratio to explore the potential role of maternal antibodies.

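### Baseline carriage is measured by qPCR in every child but has no stated role in the effect model; pre-specify it as a covariate to gain precision at almost no cost

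*Protocol*

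**What the plan says.** The Summary provides for a baseline swab in each participant: "All children will have a nasopharyngeal swab performed immediately before randomization at 4.5 months of age and eight weeks after", with a third swab at 9 months. The pneumococcal sub-study section repeats this schedule and has colonization determined by lytA PCR: "For the present study the quantitative PCR results will be used". No swab time point is left out of that statement.

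The hypothesis concerns the two later swabs, a "reduction in the risk of being colonized by *S. pneumoniae* at 6.5 and 9 months of age". The effect analysis is "Multivariate Poisson models with robust variance estimation providing prevalence ratios (PR) will be used to evaluate the effect of early MV overall", and it is also to be "stratified by potential effect modifiers: sex and presence of maternal antibodies". No covariate is listed for the models.

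The only use given to baseline data is descriptive testing between arms: "Baseline characteristics of the treatment groups will be compared using chi square tests for contingency data and t tests for continuous data".

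The Early MV trial section describes the allocation: "Infants are randomized by block randomization procedures, stratified by sex". Baseline carriage is not a stratification factor.

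**The concern.** One of the three swabs per child, 630 of 1,890 if all are taken, measures the outcome before allocation. The analysis text names the model, the variance estimator, the effect measure, the significance level and two effect modifiers, but gives this measurement no part in estimating the effect.

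Two things are at stake. First, if earlier carriage predicts later carriage, a model without it has a wider confidence interval than the collected data allow. Second, the arms can differ in baseline carriage by chance, and part of any such difference carries into the 6.5- and 9-month comparisons in the trial as actually realized. Both matter more in the smaller sex and antibody subgroups.

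The unlisted covariate set, placed next to baseline significance tests, also leaves it open whether adjustment is decided before or after imbalances are seen.

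**Working it through.** **Inputs from the Protocol.** Control carriage: "we assume that the prevalence in the control group will be 85" per cent. Early MV carriage 75%; 420 early MV and 210 control children; 80% power; P<0.05 (Sample size calculations and Statistical analysis).

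**Assumed inputs.** A two-sided test, because sidedness is not stated. Baseline carriage of 85%, carried over from the control assumption. The correlation phi between baseline and follow-up carriage, which the Protocol does not give; the main range is 0.1 to 0.4.

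**1. The stated sample size.** For two proportions at 2:1 allocation, the pooled rate is (0.85×210 + 0.75×420)/630 = 0.7833. Without continuity correction:

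n(control) = [1.96×√(1.5×0.7833×0.2167) + 0.8416×√(0.85×0.15 + 0.75×0.25/2)]² / 0.10² = 192, with 384 early MV.

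With continuity correction it is 207 and 414, which reproduces 210 and 420 to within 3%. The stated power therefore does not depend on baseline adjustment.

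**2. Unadjusted power at 210 and 420.**
- Pooled SE = √[0.7833×0.2167×(1/210 + 1/420)] = 0.0348.
- Unpooled SE = √(0.1275/210 + 0.1875/420) = 0.0325.
- Power = Φ[(0.10 − 1.96×0.0348)/0.0325] = 83.6%.

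**3. Gain from adjustment.** Residual variance is multiplied by about 1 − phi², which is equivalent to 630/(1 − phi²) children.

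| phi | variance cut | equivalent children | pooled power |
|---|---|---|---|
| 0 | 0% | 630 | 83.6% |
| 0.1 | 1% | 636 | 84.0% |
| 0.2 | 4% | 656 | 85.1% |
| 0.3 | 9% | 692 | 87.0% |
| 0.4 | 16% | 750 | 89.6% |

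**4. Check with the planned model.** Robust Poisson models were simulated with and without baseline carriage, 4,000 runs per phi.

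| phi | power unadjusted | power adjusted | SD of log PR unadjusted | SD of log PR adjusted |
|---|---|---|---|---|
| 0.1 | 85.9% | 86.3% | 0.0407 | 0.0405 |
| 0.2 | 85.9% | 87.2% | 0.0410 | 0.0402 |
| 0.3 | 86.7% | 89.2% | 0.0407 | 0.0387 |
| 0.4 | 86.5% | 91.7% | 0.0402 | 0.0372 |

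The average prevalence ratio was about 0.88 with and without adjustment (true value 0.75/0.85 = 0.882), so adjustment does not change what is estimated. At phi 0.4 the variance ratio is (0.0372/0.0402)² = 0.86, close to the 0.84 from the formula.

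**5. Chance imbalance.**
- SD of the baseline difference = √[0.85×0.15×(1/420 + 1/210)] = 0.0302, or 3.0 points; 95% range ±1.96×3.02 = ±5.9 points.
- Chance of a difference beyond 5 points in either direction: 5/3.02 = 1.66 SD, about 10%.
- Carry-over is about phi × imbalance. For 5 points this is 0.1×5 = 0.5 to 0.4×5 = 2 points, against the 10-point effect sought.
- In one sex, taken as half of each arm, the SD becomes 3.02×√2 = 4.3 points.

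**The case against.** The strongest reply is that the Protocol nowhere says baseline carriage is left out. It calls the models multivariate, which most naturally means that they have terms beyond treatment, and a covariate list is often placed in a statistical analysis plan, which is not shown here. This stands. A reader might infer that the plan discards the baseline result; the text supports only that its use is not specified.

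A reader might also infer that baseline differences bias the treatment estimate. They do not. After randomization they are chance differences, the unadjusted ratio is unbiased, and its confidence interval already allows for them. Nor does a 5-point imbalance pass through in full: only about phi times it does.

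The reply is also right that the benefit depends on a correlation the Protocol does not give. At phi 0.1 the power gain is 0.4 points (83.6% to 84.0%), which is negligible, and it becomes material only from about 0.3. That baseline carriage is the strongest predictor of later carriage is plausible but not shown.

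Finally, log10 lytA load is undefined for PCR-negative children, about 0.15×630 ≈ 95 at the assumed carriage. A complete-case model would also drop children with a missing or inhibited baseline result, contrary to the intention-to-treat statement. This limits the fix to binary carriage with a rule for missing values.

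What remains is a specific improvement: the measurement is already planned in every child, and using it costs one model term.

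**Conclusion.** The point holds as a matter of efficiency and pre-specification. The analysis text gives no role to an outcome measurement that is planned in every child before allocation and is not balanced by design.

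Under an assumed phi of 0.1 to 0.4, adjustment would cut variance by about 1 to 16%, worth 6 to 120 extra children. Pooled power would be about 84 to 90% instead of 83.6%. It would also remove a conditional shift of about 0.5 to 2 points should a 5-point imbalance occur, which has about a 10% chance at an assumed 85% baseline carriage.

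A reader might go further and infer that the trial is underpowered or its planned estimate invalid without this adjustment. The documents do not support that: the stated sample size reproduces without any adjustment, and the unadjusted analysis is valid. The size of the gain is uncertain because phi is unknown; its direction is not in doubt if earlier carriage predicts later carriage at all.

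**What to change.** In the Statistical analysis text of the pneumococcal sub-study:

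- Name baseline qPCR carriage (yes/no) as a pre-specified covariate in the Poisson models for 6.5 and for 9 months, both overall and in the sex and maternal-antibody analyses.
- Keep children with a missing or inhibited baseline PCR result through a missing-indicator category, so that no randomized child is lost because of the covariate. This is sound here because the sample predates allocation.
- Report the unadjusted prevalence ratio alongside.
- Treat baseline log10 lytA load as optional, and use it only with a stated value for PCR-negative children.

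The cost is a few sentences and one more model term (two parameters with the missing category). No further swabs or assays are needed. If phi turns out low, little is gained and little is lost: at phi 0 simulated power was 86.2% adjusted against 86.3% unadjusted.

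### The hypothesis names two follow-up swabs of equal standing, but the significance rule and the 80% power fit one comparison at a visit the protocol does not name

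*Protocol*

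**What the plan says.** Under the heading for the pneumococcal sub-study, the Objective plans a baseline swab and then two more, "and at 6.5 and again at 9 months of age (immediately before MV"). The Hypothesis is a lower risk of colonization "at 6.5 and 9 months of age". Neither visit is called primary there or in the Summary.

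The Statistical analysis paragraph plans Poisson models with robust variance giving prevalence ratios, for all children and by sex and presence of maternal antibodies as possible effect modifiers. The decision rule is one sentence: "Differences will be considered significant at P<0.05". The text does not say whether the two follow-up visits are tested separately or together, or whether one or both must be significant.

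The Sample size paragraph takes 420 vaccinated children and 210 controls and concludes: "we will be able to show a reduction from 85% to 75% associated with early MV with a power of 80% and p<0.05". No visit is attached to the 85% or the 75%. The same paragraph presents the role of maternal antibodies as something to be explored.

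**The concern.** Three statements do not fit together: a hypothesis with two time points, a rule that lets any difference count at 0.05, and a power figure for one contrast. A reader cannot tell which result would confirm the hypothesis.

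If the visits are tested separately, each way of combining them breaks something the protocol states. Accepting either visit raises the error rate above 5%. Requiring both brings the power below 80%. If the choice is left open until the data are seen, the visit with the smaller P value can become the result. A SAP commonly settles the details of secondary multiplicity. Here the protocol has already fixed a blanket threshold and a power figure, and which comparison that power belongs to is protocol content.

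**Working it through.** **Inputs from the protocol.** Control carriage p1 = 0.85, early-vaccine carriage p2 = 0.75, difference 0.10, 210 controls and 420 vaccinated (ratio k = 2), significance level 0.05, power 80%.

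**Assumptions not in the protocol.** Two-sided tests; correlation r between the two visits' test statistics from 0 to 0.7; the same 10-point effect at both visits; no loss to follow-up.

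**1. Reproduce the stated figure for one comparison.**
- Average carriage: (0.85 + 2 × 0.75)/3 = 0.7833.
- A = √[(1 + 1/2) × 0.7833 × 0.2167] = 0.5046.
- B = √[0.85 × 0.15 + 0.75 × 0.25/2] = 0.4704.
- Controls needed: n = (1.960A + 0.8416B)²/0.10² = 191.8, so 192 + 384.
- With continuity correction: (n/4) × [1 + √(1 + 2(k + 1)/(n × k × 0.10))]² = 206.5, so 207 + 414. The plan has 210 + 420.
- Power at 210 + 420 without correction: Φ[(0.10√210 − 1.960A)/B] = Φ(0.978) = 83.6%. With correction it is 80.7%.
- A Wald test on the log prevalence ratio, closest to the planned analysis: ln(0.85/0.75)/√[0.15/(0.85 × 210) + 0.25/(0.75 × 420)] = 3.10, and Φ(3.10 − 1.96) = 87%.

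The stated 80% is therefore sound, for one two-sided comparison at one visit.

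**2. Separate tests, either visit suffices.** For independent tests, the chance of at least one false positive is 1 − 0.95² = 9.75%. For correlated tests it is 1 − P(|Z1| < 1.96 and |Z2| < 1.96), with Z1 and Z2 bivariate normal.

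| r | Two-sided false-positive rate |
| --- | --- |
| 0 | 9.75% |
| 0.3 | 9.5% |
| 0.5 | 9.1% |
| 0.7 | 8.3% |

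Splitting the level to 0.025 per visit removes the excess. Power per visit at 210 + 420 then falls to 75.1% without and about 71% with continuity correction. Regaining 80% would take 234 + 468 or 248 + 496 children.

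**3. Separate tests, both visits required.** The error rate does not exceed 5%. Joint power is P(Z1 < m and Z2 < m), where m = Φ⁻¹(power per visit).

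| r | From 80% per visit | From 83.6% per visit |
| --- | --- | --- |
| 0 | 64% | 70% |
| 0.3 | 67% | 72% |
| 0.5 | 69% | 74% |
| 0.7 | 71% | 76% |

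**4. One pooled test of both follow-up swabs.** The expected test statistic at one visit with 80% power is 1.960 + 0.842 = 2.80. Averaging two visits multiplies it by √[2/(1 + r)]. At r = 0 this gives 3.96 and power Φ(3.96 − 1.96) = 98%. At r = 0.7 it gives 3.04 and power 86%. The error rate is 5%.

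If the effect exists at one visit only, the pooled statistic is half as large. Its power is then Φ(1.98 − 1.96) = 51% at r = 0 and Φ(1.52 − 1.96) = 33% at r = 0.7.

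**The case against.** The strongest reply is that the protocol never says each visit is tested on its own. A joint analysis would cause no inflation. A literal reading of the hypothesis requires both visits, which also causes none. The sample size calculation is correct for what it computes, and sizing a study on one contrast is not an error. All of this stands, and the inflation is therefore conditional. It does not close the gap: a joint model is not described, since no visit term or clustering on child is mentioned, and the both-visits reading gives up the stated 80%.

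A second reply is that the hypothesis is a reduction, so only one direction matters. The chance of falsely finding a reduction at either visit is at most 1 − 0.975² = 4.9%. That is right, but the matching rate for one two-sided 0.05 test is 2.5%, so the relative excess is the same.

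Three stronger readings are tempting and not supported:
- **That the error rate doubles.** The value 9.75% is the ceiling for independent or positively correlated tests, and it applies only if either visit suffices. The same children are swabbed twice, so positive correlation is likely.
- **That the hypothesis spans ten tests with a 29% to 31% error rate.** That figure counts the overall result and four sex and antibody strata at each visit, over correlations of 0 to 0.5. The strata fall under the 0.05 sentence but are not in the hypothesis, and nothing says a stratum result would establish an effect. The antibody role is only to be explored, and the calculation needs an antibody-positive share that the protocol does not give.
- **That the 80% power belongs to the 6.5-month swab.** Nothing ties it to either visit.

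**Conclusion.** The concern holds in limited form. The protocol sets two follow-up ages on an equal footing and supplies a threshold and a power figure for one comparison. With separate tests the cost is either a two-sided error rate of about 8.3% to 9.75%, or a joint power of about 64% to 71% (70% to 76% if the uncorrected 83.6% per visit is the starting point). These ranges rest on two-sided testing, an assumed correlation of 0 to 0.7, equal effects at both visits for the power figures, and complete follow-up. The single-comparison power is not in error. This should be fixed. It is a gap in the decision rule that the planned data can close, in a mechanistic sub-study nested in a trial whose primary objective is mortality.

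**What to change.** State one primary comparison at two-sided 0.05 in the Statistical analysis paragraph, and say in the Sample size paragraph that the power refers to it.

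- **Preferred:** one Poisson model on both follow-up swabs, with a visit term and variance clustered on child. The visit-specific prevalence ratios become secondary.
- **Alternative:** the sponsor names one visit as primary, attaches the 80% power to it, and tests the other visit only if the first is significant.

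In either case, report the sex and maternal-antibody strata as exploratory. This agrees with how the protocol already describes the antibody role.

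The cost is about one paragraph of text, with no extra children or swabs. The pooled prevalence ratio averages over the two visits and would dilute an effect present at only one, as step 4 of the working shows. With a named visit, a claim at the other visit becomes conditional on the first. The choice should be fixed before outcome data are compared by arm.
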